#### Analysis of secondary outcomes

Secondary outcomes will be compared in the intention-to-treat cohort only using a chi-square test. Results will be reported using RR and 95% CI.

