### Study population

A flow chart will be constructed according to the CONSORT guidelines (Fig. 1). We will report the number of patients who were screened, met inclusion or exclusion criteria, and were eligible but not enrolled and reasons for non-enrollment. We will report the number of patients who were randomized to each group, received the allocated intervention, and had at least one ultrasonography performed.

*The Intention-to-treat population* consists of all enrolled patients and will be used for the primary analysis. All enrolled patients will be included regardless of whether or not they received the allocated intervention or had an ultrasonography performed. Post-enrollment exclusion from the intention-to-treat analysis will be restricted to withdrawal of consent to use trial data by the patient or surrogate decision-maker (SDM). However, if the patient or SDM withdraws consent for trial participation but permits collection and use of data, we will include these participants in the planned intention-to-treat analysis. Patients will also be excluded post enrollment if the eligibility criteria were not met. We plan to enroll additional patients to compensate for patients who are excluded post randomization.

*The per-protocol population* consists of all randomized patients who received the allocated intervention *and* had at least one ultrasonography performed. Although the protocol requires that a baseline ultrasonography is performed, enrolled patients may infrequently not have a single trial ultrasonography performed. For example, this circumstance may occur if a patient dies or is transferred out of the participating ICU before an ultrasonography can be performed, if the patient’s ICU stay was shorter than expected (< 72 h) or if there was to difficulty scheduling ultrasonography over weekends.

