### Intervention data

For each group we will report details regarding IPC use and the average daily duration of use (excluding study first and last days because they are usually less than 24 h, Additional file 1: Table S2). We will report reasons for not using IPCs in the IPC group and reasons for IPC use in the control group. We will classify these events as per-protocol and not per-protocol. We will classify IPC devices as sequential or non-sequential and will report the use of thigh- or knee-length sleeves and the use of foot pumps.

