***Non-lower-extremity thrombosis***
5.***Lower-extremity skin pressure ulcers.*** This is a safety outcome, testing whether IPC increases the risk of skin pressure ulcers defined according to the National Pressure Ulcer Advisory Panel (NPUAP) classification6.***Lower-extremity ischemia.*** This is a safety outcome, testing whether IPC increases the risk of ischemia in the lower extremities by compromising blood flow7.***Serious adverse events (SAEs)*** defined in the study protocol as skin pressure ulcers of categories III and IV or ischemia due to IPC [5]8.***Non-tolerance to IPC*** defined as not using IPC for one calendar day or more because of discomfort9.Mechanical ventilation duration and mechanical-ventilation-free days, vasopressor therapy duration and vasopressor-free days, ICU stay and ICU-free days and hospital length of stay (LOS)10.

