#### Analysis of primary outcome

The primary outcome will be compared in the intention-to-treat and per-protocol cohorts (effectiveness analysis) using chi-square test. Results will be reported as RR with 95% CI (Additional file 1: Table S5). Because some centers may have few events, we will use a generalized linear mixed-model (GLMM) used to estimate adjusted RR after incorporating center/site as random effect [14]. If there is significant difference, we will report relative risk reduction (RRR), absolute risk reduction (ARR) or increase, and number needed to treat (or harm) with 95% CIs. The unadjusted Cox proportional hazard model will also be used to test the null hypothesis and will be used as a secondary analysis tool. We define the hazard function at time *t* as the instantaneous probability of a DVT at time *t* given the patient was free of DVT up to that time. Incident DVT cases will be considered as events. Specifically, we will censor patients who are free of DVT by the end of the 28-day follow-up period, those who die before day 28, and those lost to follow-up (dropouts and lost to follow-up before day 28). We will report hazard ratio (HR) with 95% CI. Kaplan-Meier curves will be generated for the alternative treatment groups and a log-rank test will be used to compare distributions. Although imbalances in baseline characteristics are unlikely with the large sample size, we will conduct an adjusted Cox proportional hazard model with center/site as random effect to adjust for the following factors (defined a priori): enrollment center and type of heparin used (unfractionated vs. low-molecular-weight), in addition to the following variables that are strongly believed to have significant impact on DVT incidence, source of admission to ICU being the ward (compared to the emergency department, operating room and others), trauma, femoral line, dialysis and heart failure.

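### Pressure ulcers, limb ischemia and SAEs get only an intention-to-treat comparison, which tends to dilute a real device harm; a supportive analysis by IPC actually received should stand beside it.

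*Protocol article*

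**What the plan says.** **Outcomes.** In the article's Secondary outcomes section, item 5 (pressure ulcers) reads "This is a safety outcome, testing whether IPC increases the risk of skin pressure ulcers" and item 6 reads "This is a safety outcome, testing whether IPC increases the risk of ischemia in the lower extremities by compromising blood flow". Item 7 defines SAEs as "skin pressure ulcers of categories III and IV or ischemia due to IPC". All three are secondary outcomes.

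**Analysis.** Analysis of secondary outcomes states: "Secondary outcomes will be compared in the intention-to-treat cohort only using a chi-square test". In Table 1 the per-protocol cell of the secondary-outcomes row is None. For the primary outcome, by contrast: "The primary outcome will be compared in the intention-to-treat and per-protocol cohorts (effectiveness analysis) using chi-square test". Sensitivity analyses adds a dose-effect analysis relating IPC duration to incident proximal DVT.

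**Cohorts.** For the intention-to-treat cohort, Study population says: "All enrolled patients will be included regardless of whether or not they received the allocated intervention or had an ultrasonography performed". The per-protocol cohort "consists of all randomized patients who received the allocated intervention" and also had at least one ultrasonography.

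**Departures from allocation.** Under Intervention data: "We will report reasons for not using IPCs in the IPC group and reasons for IPC use in the control group". The same section reports average daily duration of IPC use by group. Item 8 of the secondary outcomes counts patients who go a calendar day or more without IPC because of discomfort.

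**The concern.** Harm caused by a compression sleeve needs exposure to the sleeve. The plan anticipates patients in the IPC arm who do not use it and controls who do. Both kinds of patient make the randomized arms more alike in exposure, so a true harm shows up in the intention-to-treat comparison as a smaller risk ratio.

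For a claim of benefit that attenuation is conservative. For a harm question it works the other way, because it favours finding no difference. The report could then show no clear excess of ulcers or ischemia partly because the device was not worn as allocated, and readers could take this as reassurance about the device itself.

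The restriction is a stated choice, in the text and again in Table 1, so it is not a detail left to another document. The exposure data needed to look further are recorded, but the plan relates them only to the primary outcome.

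**Working it through.** **What the plan gives.** It gives no ulcer or ischemia rate, no expected non-use and no expected crossover, so it has no figure of its own on this point to reproduce. Its only power statement (80% for DVT at 7% versus 4%) concerns a different outcome. It is consistent with 2000 patients: a continuity-corrected two-proportion formula at two-sided 5% needs 971 per arm, or 1942.

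**Inputs.**
- From the article: 2000 patients, two-sided 5% tests.
- Assumed: equal allocation (1000 per arm), harm risk 2% without IPC and 4% with IPC (true risk ratio 2.0), all-or-none exposure, and non-use unrelated to a patient's underlying risk.

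**Formulas.** Let a be the share of the IPC arm not exposed and c the share of controls exposed.
- IPC-arm risk: p1 = (1 − a) × 0.04 + a × 0.02
- Control risk: p0 = (1 − c) × 0.02 + c × 0.04
- Power = Φ[(d − 1.96 × se0) / se1], where d = p1 − p0, se0 uses the pooled risk and se1 the separate risks.

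With no departures: d = 0.02, se0 = √(0.03 × 0.97 × 2/1000) = 0.00763, se1 = √((0.04 × 0.96 + 0.02 × 0.98)/1000) = 0.00762. Power = Φ(0.66) = 75%.

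| Departures | p1 | p0 | ITT risk ratio | Power |
|---|---|---|---|---|
| None | 4.0% | 2.0% | 2.00 | 75% |
| 5% non-use, IPC arm only | 3.9% | 2.0% | 1.95 | 71% |
| 10% non-use, IPC arm only | 3.8% | 2.0% | 1.90 | 67% |
| 20% non-use, IPC arm only | 3.6% | 2.0% | 1.80 | 58% |
| 5% in both arms | 3.9% | 2.1% | 1.86 | 66% |
| 10% in both arms | 3.8% | 2.2% | 1.73 | 55% |
| 20% in both arms | 3.6% | 2.4% | 1.50 | 35% |

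**A second set of assumptions.** With 3% risk without IPC, a true ratio of 2.0 and unequal departures:
- a = 5%, c = 2%: ratio 1.91, power 86%
- a = 10%, c = 5%: 1.81, 79%
- a = 20%, c = 10%: 1.64, 63%
- a = 30%, c = 10%: 1.55, 52%
- no departures: 2.00, 90%

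The direction is the same throughout. The size depends on adherence and, strongly, on how many controls receive IPC.

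**Would the existing per-protocol cohort solve it?** No. Suppose there is no true harm, the risk is 4% in both arms, and 20% of the IPC arm are excluded as non-wearers whose risk is k times the average. The risk left in the IPC arm is 0.04 × (1 − 0.2k)/0.8.
- k = 2: 0.04 × 0.6/0.8 = 3.0%, ratio 0.75
- k = 0.5: 0.04 × 0.9/0.8 = 4.5%, ratio 1.13

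Dropping non-wearers can therefore create false reassurance or a false signal. The cohort's ultrasonography condition also has no bearing on skin or limb harm.

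**The case against.** **Intention to treat is valid for harm.** It is the randomized comparison, and nothing in the plan is misstated or contradictory here. This stands, and it is why intention to treat should remain the main analysis. The point is only that nothing based on exposure stands beside it.

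**A reader might infer that the plan examines benefit more closely than harm.** The article does not support that. Only the primary outcome gets the per-protocol and duration analyses. Secondary benefit outcomes, such as PE, all lower-extremity DVT and the composite with mortality, are also analysed by intention to treat alone. The line runs between primary and secondary outcomes.

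**A reader might also infer that every spell without IPC dilutes the harm estimate.** It does not. If the sleeve is removed because an ulcer has formed, intention to treat still counts that ulcer.

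**Part of the need is already met.** Duration of use and reasons for departures will be reported by group, so readers can gauge how much dilution is possible. The SAE definition ties ischemia to IPC, and non-tolerance is itself an outcome. This helps, but none of it relates exposure to the occurrence of ulcers or ischemia.

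**The magnitude is assumed, and the remedy has its own bias.** Both are true. Anticipating departures does not show that they are common. A comparison by IPC received is open to selection and reverse causation, and classifying patients by any receipt does not correct for partial daily non-use. Such an analysis can support the interpretation but cannot overrule the randomized result.

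**Conclusion.** The point holds as a modest, inexpensive improvement. The plan confines pressure ulcers, ischemia and SAEs to an intention-to-treat comparison, which tends to understate a real device harm when allocation and use diverge.

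The size is unknown. Under the assumed 2% versus 4% with 1000 per arm, a true ratio of 2.0 appears as 1.95 to 1.80 (power 71% to 58%, against 75%) with 5% to 20% non-use in the IPC arm only. With equal crossover in both arms it appears as 1.86 to 1.50 (power 66% to 35%). At high adherence and little control-arm use the effect is small. The article does not support saying that the trial will miss a harm, nor that intention to treat is the wrong main analysis for safety.

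**What to change.** Keep intention to treat as the main safety comparison. For pressure ulcers, ischemia and SAEs only, amend Analysis of secondary outcomes and the Table 1 per-protocol entry to add a prespecified supportive analysis:

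- Classify patients by IPC actually received, without requiring an ultrasonography.
- Count only exposure before the event, so that IPC stopped because of an ulcer is not misclassified as non-use.
- Give events per 100 IPC-days as a description for exposed patients. Unexposed controls have no such denominator, so this is not a between-arm comparison.
- Report the results beside intention to treat, labelled as not protected by randomization.
- State that a null intention-to-treat result alone will not be read as evidence that the device is harmless. Do not require the two analyses to agree, because that would give the more bias-prone one a veto.

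The cost is a short amendment and a few table rows from IPC-use data already being recorded. The article reports 1620 of 2000 patients enrolled as of January 2018, so the addition could be fixed before database lock. The downside is possible confounding and reverse causation in the added analysis, which the label should make plain.

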### Statistical analysis

Categorical variables will be reported as numbers and frequencies, and will be compared using the chi-square test. Continuous variables will be reported as mean and standard deviation or median and interquartile ranges (IQR, Q1–Q3). Continuous variables will be tested using the Student’s *t* test or the Wilcoxon-Mann-Whitney test, as judged appropriate by normality testing. For serial measurements, we will test the change over time and the difference between the two groups over time using a repeated-measures analysis of variance, with no imputation for missing values. For serial measurements, we will use the Bonferroni correction to account for multiple comparisons. Associations will be reported as risk ratios (RR) or hazard ratios (HR) with 95% CIs. Unless otherwise specified, tests will be two-sided and at the 5% significance level. All statistical analyses will be conducted using the SAS software version 9.1.3 or higher (SAS Institute, Cary, NC, USA).

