#### Sensitivity analyses

In a sensitivity analysis, we will consider all lower-extremity DVT and PE events as incident. In another sensitivity analysis, we will consider post-enrollment lower-extremity DVT and PE events if they occur on calendar day 2 or later post enrollment [13]. Because mortality can be a competing outcome with VTE, we plan a sensitivity analysis that is restricted to patients who survive and in the ICU for at least 14 days. Because baseline ultrasonography can be missing, some patients may have a positive non-baseline ultrasonography without a baseline ultrasonography examination, making it difficult to determine whether DVT was a prevelent or an incident event. In these patients, we will have a sensitivity analysis assuming that the missing baseline ultrasonography was negative for DVT and another analysis assuming that the exam was positive. We will examine dose-effect relationship by assessing the relationship of the IPC duration and incident proximal lower-extremity DVT (Table 1 and Additional file 2: SPIRIT 2013 Checklist).

**Table 1 Tab1:** Summary of analysis plan

Variables	Intention-to-treat cohort	Per Protocol cohort
Baseline characteristics	No statistical comparisons will be performed	None
Intervention and co-interventions	Chi-square, Fisher’s exact test, Mann-Whitney *U* test, *t* test as applicable	None
Primary outcome	1. Primary analysis: chi-square. Report relative risk. Generalized linear mixed model (GLMM) incorporating center/site as random effect. Report as adjusted relative risk. If a significant difference detected: relative risk reduction, absolute risk reduction and number needed to treat (or harm) will be reported 2. Secondary analyses: unadjusted Cox proportional analysis, Kaplan-Meier (KM) curves, adjusted Cox proportional analysis	1. Primary analysis: chi-square and relative risk. Generalized linear mixed model (GLMM) incorporating center/site as random effect. Report as adjusted relative risk. If a significant difference detected: relative risk reduction, absolute risk reduction and number needed to treat (or harm) will be reported. 2. Secondary analyses: unadjusted Cox proportional analysis, KM curves, adjusted Cox proportional analysis
Secondary outcomes	Chi-square. Report relative risk	None
Subgroup analyses	Chi-square. Report relative risk	None

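### Rare safety outcomes have RR as their only planned between-group estimate, so the plan may give no pre-specified upper bound on IPC harm; add a risk difference with a score-based CI

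*Protocol article*

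**What the plan says.** The article presents itself as the trial's analysis plan.

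- **Analysis of secondary outcomes** sets the method: "Secondary outcomes will be compared in the intention-to-treat cohort only using a chi-square test. Results will be reported using RR and 95% CI". The secondary outcomes row of Table 1 repeats it: "chi-square. Report relative risk".
- **Secondary outcomes, items 5 to 7**, place the harm outcomes under that rule. These are lower-extremity pressure ulcers, lower-extremity ischemia ("testing whether IPC increases the risk of ischemia in the lower extremities by compromising blood flow") and SAEs ("defined in the study protocol as skin pressure ulcers of categories III and IV or ischemia due to IPC").
- **Statistical analysis** adds description: "Categorical variables will be reported as numbers and frequencies, and will be compared using the chi-square test". For comparisons it says: "Associations will be reported as risk ratios (RR) or hazard ratios (HR) with 95% CIs".
- **Analysis of primary outcome** is the only place with absolute measures, and there they are conditional: "If there is significant difference, we will report relative risk reduction (RRR), absolute risk reduction (ARR) or increase, and number needed to treat".

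The article gives no expected rate for any safety outcome, no risk difference for them, and no rule for an arm with no events.

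**The concern.** For a harm outcome, the main result is usually the largest excess risk that the data still allow. A ratio supplies this only if the comparator has events. The control arm is the one more likely to be empty if IPC does cause ischemia, so the planned measure fails in the direction that matters.

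The benefit is sized on the absolute scale (7% to 4%, in the Abstract). A reader weighing IPC needs the harm on that scale too, with an interval chosen in advance. If the interval is chosen after the counts are known, its method becomes a post-hoc decision.

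**Working it through.** **Inputs.** Total sample 2000 (Study design). Equal allocation, hence 1000 per arm, is assumed because the ratio is not stated. DVT rates 7% vs 4% and 80% power are from the Abstract. Safety event rates are not given, so a range is assumed, equal in both arms.

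**1. The plan's own figure.** n per arm = [1.960·√(2·0.055·0.945) + 0.842·√(0.07·0.93 + 0.04·0.96)]² / 0.03² = 906, total 1812. With continuity correction it is 971 per arm, total 1942, within 3% of 2000. Power at 1000 per arm is 83.8% uncorrected and 81.2% corrected. So 1000 per arm and a 3-point benefit are a fair frame.

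**2. Chance of an empty arm.** With risk r, q = (1 − r)^1000 is the chance that the control arm is empty, q² that both are, and 2q − q² that at least one is.

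| Assumed risk | Expected events per arm | Control empty | Both empty | At least one empty |
|---|---|---|---|---|
| 0.05% | 0.5 | 61% | 37% | 85% |
| 0.1% | 1 | 37% | 14% | 60% |
| 0.2% | 2 | 14% | 2% | 25% |
| 0.3% | 3 | 5% | 0.2% | 10% |
| 0.5% | 5 | 0.7% | about 0% | 1.3% |
| 1% | 10 | about 0% | about 0% | about 0% |

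The control-empty column is the relevant one for a harm limit.

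**3. What the RR gives (IPC vs control events, 1000 per arm).**

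- 3 vs 0: the score (Koopman) interval has lower limit 0.78 and no finite upper limit.
- 0 vs 0: no RR.
- 0 vs 3: RR 0, with a finite score upper limit of 1.28. For 0 vs 1 it is 3.84.
- Adding 0.5 to each count makes 3 vs 0 finite, but the result is RR 7.0 (0.36 to 135.3), which depends heavily on the added constant. The article plans no such correction.

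**4. What a risk difference gives.** Newcombe limits, with Wilson limits l and u for each arm's risk p and d = p₁ − p₂:

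lower = d − √[(p₁ − l₁)² + (u₂ − p₂)²]; upper = d + √[(u₁ − p₁)² + (p₂ − l₂)²].

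For 0/1000, l = 0 and u = 3.8415 / 1003.8415 = 0.383%.

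| IPC vs control | Difference (points) | 95% CI (points) |
|---|---|---|
| 0 vs 0 | 0 | -0.38 to +0.38 |
| 3 vs 0 | 0.3 | -0.13 to +0.88 |
| 5 vs 0 | 0.5 | +0.02 to +1.17 |

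Each upper limit is finite and can be set directly beside the 3-point benefit.

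**The case against.** **Counts per arm will be published.** This stands. A reader might infer that RR is all that will be shown, but Statistical analysis promises numbers and frequencies. From 0/1000, an exact upper limit on the IPC-arm risk follows: 1 − 0.025^(1/1000) = 0.37%. What is missing is a between-group interval fixed in advance, not the data for one.

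**The CI method is left open, so an RR interval need not fail whenever an arm is empty.** This stands for an empty IPC arm (step 3). It does not rescue an empty control arm, and the figures for at least one empty arm should not be used to size the problem.

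**Rarity is assumed.** This stands. At 0.5% or more the problem nearly vanishes. SAEs include category III and IV ulcers, which control patients can also have. On the other hand, the ischemia component is tied to IPC by definition, so for that part control events would be expected mainly through crossover.

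**The chi-square rule is shorthand.** This stands. Durations and serial scores are also secondary outcomes, and the general methods cover those. The point concerns binary safety outcomes only.

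Two stronger readings are tempting:

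- A reader might infer that chi-square must give way to Fisher's exact test, since Table 1 names the latter ("Chi-square, Fisher’s exact test") for co-interventions only, and 5 vs 0 gives p = 0.025 by chi-square and 0.062 by Fisher. But the chi-square type I error, enumerated for 4 to 10 expected events in total, is 4.1% to 4.7%. It is not inflated, and replacing it would be a preference.
- A reader might add PE with cardiopulmonary complications. The article lists it among the PE outcomes, not as a safety outcome of IPC, so it has no bearing on a limit for harm.

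Additional file 1 is not shown and may say more, although its Table S4 is described as listing outcomes with definitions.

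**Conclusion.** The point holds in limited form. For the binary safety outcomes, the article fixes RR with 95% CI as the only between-group estimate, and that estimate can lose its upper limit or not exist. With 1000 per arm and equal risks, both assumed, the chance of an empty control arm is 37% to 5% over assumed risks of 0.1% to 0.3%, and below 1% at 0.5%.

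The consequence is a possible absence of a pre-specified upper bound on IPC harm. The primary analysis is unaffected, no data are lost, and no passages contradict each other. If pressure ulcers prove frequent, their RR interval will exist and the gain is only the absolute scale.

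**What to change.** In Analysis of secondary outcomes and the secondary outcomes row of Table 1, add that for lower-extremity pressure ulcers, lower-extremity ischemia and SAEs the absolute risk difference (IPC minus control) will be reported with a score-based 95% CI, whatever the significance. Name one method, Newcombe or Miettinen-Nurminen. Keep the RR with CI where both arms have events, and leave the chi-square test as it is.

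The cost is one sentence, one table cell and one more reported estimate per outcome. It needs no new data. Recruitment stood at 1620 of 2000 in January 2018, and the authors are to stay blinded until database lock, so the addition can still be pre-specified.

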### Analysis plan

#### Baseline characteristics

We will present baseline characteristics in the two groups of the intention-to-treat cohort (Additional file 1: Online Supplement Table S1). We will compare age, sex, weight, height and Body Mass Index (BMI) between the two study groups. We will compare location immediately prior to ICU admission, Acute Physiology And Chronic Health Evaluation (APACHE) II scores, admission categories, and chronic illnesses as defined by the APACHE II system [10]. We will compare the two groups for the history of heart failure as per New York Heart Association classification and by ejection fraction (if echocardiographic assessment is performed). We will compare pre-defined pre-ICU VTE risk factors, including personal history of VTE, family history of VTE, known thrombophilic states (protein C, protein S or antithrombin deficiency, thrombotic thrombocytopenic purpura, hemolytic-uremic syndrome, activated protein C resistance, factor V Leiden thrombophilia, prothrombin gene mutation, antiphospholipid antibody, hyperhomocysteinemia), post-partum status (within 3 months), estrogen therapy (oral contraceptive or hormone replacement), active malignancy (treatment within the past 6 months or palliation), history of malignancy (within the past 5 years, other than non-melanoma skin cancer), paralysis or immobilization of a lower or upper extremity related to stroke or injury prior to this hospital admission, hospitalization in the past 3 months for any reason (excluding this hospital admission), trauma (including acute spinal cord injury, hip fracture, pelvic fracture, femoral fracture and tibial, fibular, knee or other fractures below knee), recent surgery (in the last 48 h) and acute stroke (in this index hospital admission). We will compare baseline platelet count, international normalized ratio (INR), partial thromboplastin time (PTT), creatinine and partial pressure of arterial oxygen/fraction of inspired oxygen (PaO_2_/FiO_2_) ratio. We will also compare the two study groups for mechanical ventilation, and use of vasopressors, presence of central venous catheters or dialysis catheters in the jugular, subclavian or upper extremities or in the femoral veins. We will compare the number of days from ICU admission and enrollment and use of IPC prior to randomization and duration of use.

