***Mortality outcomes assessed at ICU discharge, 28 days, hospital discharge and 90 days***
11.***Composite outcome of lower-extremity DVT, PE and 28-day mortality***
**to** address the competing risk of VTE and mortality [12, 13]12.Serial respiratory, cardiovascular Sequential Organ Failure Assessment (SOFA) scores13.Serial daily fluid intake, output and balance and vasopressor doses

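### Mortality and the DVT/PE/28-day death composite are compared by crude chi-square only, which is valid but leaves collected prognostic data unused and gives up a modest amount of precision

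*Protocol article*

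**What the plan says.** Under *Analysis of secondary outcomes* the article says: "Secondary outcomes will be compared in the intention-to-treat cohort only using a chi-square test". It adds: "Results will be reported using RR and 95% CI". The secondary-outcome row of Table 1 names the same method, "chi-square. Report relative risk", and no model.

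The secondary outcomes include "Mortality outcomes assessed at ICU discharge, 28 days, hospital discharge and 90 days" and the "Composite outcome of lower-extremity DVT, PE and 28-day mortality". The article introduces the composite as its way of handling death as a competing risk for VTE.

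*Baseline characteristics* shows that age and "Acute Physiology And Chronic Health Evaluation (APACHE) II scores, admission categories, and chronic illnesses" are recorded in both arms, as are ventilation and vasopressor use. *Subgroup analyses* says that randomization is stratified by heparin type.

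Model-based estimates are planned for the primary outcome (*Analysis of primary outcome*): a mixed model with a center effect, and a Cox model adjusted for center, heparin type and variables "strongly believed to have significant impact on DVT incidence". APACHE II and age are not among these, and no covariate is assigned to any secondary outcome.

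**The concern.** The plan accepts covariate adjustment for DVT but not for death, where baseline severity is likely to be prognostic. A crude RR leaves in its standard error the outcome variation that a baseline score could explain. Adjustment recovers part of it even when the arms are perfectly balanced. The article's remark that imbalances are unlikely in a large sample therefore does not settle the matter.

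What is at stake is the width of the interval on four mortality outcomes and on the composite meant to support the reading of the primary result. The validity of those comparisons is not in question.

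**Working it through.** **The plan's own figure.** The abstract gives 80% power for proximal DVT of 7% against 4%; the trial enrolls 2000. Two-sided alpha 0.05, 1:1 allocation assumed:

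n per arm = [1.96·√(2·0.055·0.945) + 0.8416·√(0.07·0.93 + 0.04·0.96)]² / 0.03² = (0.632 + 0.271)² / 0.0009 ≈ 906, total 1812.

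With continuity correction this is 971 per arm, total 1942 (1966 at alpha 0.048). Power at 1000 per arm with the correction is about 81%. The stated design reproduces. No size or power is given for mortality or the composite.

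**Inputs.** From the article: 2000 patients, crude RR, the baseline variables. Assumed, because the article gives no figures: 1000 per arm, mortality p, and one baseline score whose strength is expressed as an AUC.

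**Formulas.**
- Crude SE(log RR) near RR 1 = √[2(1−p)/(1000p)].
- Adjusted, standardized SE ≈ crude SE × √(1−R²), where R² = Var(m)/[p(1−p)] and m is the risk given the score (logistic in a standard normal score with slope b).

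**Mortality.** At p = 0.25 the crude SE is √(1.5/250) = 0.0775, so the CI around RR 1 is 0.859 to 1.164. At p = 0.16 it is √(1.68/160) = 0.1025, CI 0.818 to 1.222.

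| p | b | AUC | R² | CI narrower (formula) | Simulated variance ratio | CI narrower (simulated) |
|---|---|---|---|---|---|---|
| 0.25 | 0.8 | 0.70 | 0.102 | 5.3% | 0.92 | 1−√0.92 = 4.1% |
| 0.25 | 1.0 | 0.74 | 0.147 | 7.7% | 0.85 | 1−√0.85 = 7.8% |
| 0.16 | 0.9 | 0.73 | 0.100 | 5.1% | 0.91 | 1−√0.91 = 4.6% |
| 0.25 | 0.4 | 0.61 | 0.029 | 1.5% | – | – |

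The simulation used 1500 replicates of 2000 patients. A second run gave ratios of 0.91, 0.85 and 0.92 for the first three scenarios taken together, in line with these. At p = 0.25 and AUC 0.74 the adjusted SE is 0.0775 × √0.853 = 0.0715, CI 0.869 to 1.151.

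**Wider range.** Over mortality of 15% to 40% and AUC 0.60 to 0.80, the narrowing runs from 0.8% to 14.2%.

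**Bias check.** In 2000 replicates at 30% against 26% deaths (true log RR −0.143), the crude and adjusted estimates both averaged between −0.142 and −0.144. Power rose from about 51% to 54%, 56% and 57% for AUC of about 0.65, 0.70 and 0.75.

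**Composite.** Suppose DVT or PE occurs in q = 9% (assumed), independently of the score. Then composite risk = q + (1−q)m, p_c = p + q(1−p), and R²_c = (1−q)²·R²·p(1−p)/[p_c(1−p_c)].
- p = 0.25: p_c = 0.3175. With R² = 0.102, R²_c = 0.8281·0.102·0.1875/0.2167 = 0.073, so 3.7% narrower. With R² = 0.147, R²_c = 0.105, so 5.4% narrower.
- p = 0.16: p_c = 0.2356, R²_c = 0.062, so 3.1% narrower.

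**The case against.** The strongest reply is that nothing here is wrong. Under randomization the crude RR is unbiased, its interval has the right coverage, and the trial was sized for proximal DVT and not for death. That stands.

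The gain is also small on the reported scale. At 25% mortality and AUC 0.74, each confidence limit moves by about 0.01. Expressed as patients, variance ratios of 0.92 and 0.85 equal 8.7% and 17.6% more (1/0.92 − 1 and 1/0.85 − 1), but that is the same modest narrowing in a larger-sounding unit. The size rests on assumed inputs and nearly vanishes with a weak score. This stands too.

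A reader might infer that the mortality results would be biased by a chance difference in severity between arms. The documents do not support that: the crude interval already allows for chance imbalance, and severity will be reported by arm. Nor do they establish that APACHE II is a strong predictor in this population, or that the composite would gain as much as mortality. Its DVT and PE components dilute the gain.

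It could be said that an article condenses the full plan, and supplementary Tables S4 and S5 are not shown. That carries little weight here. The article presents itself as the analysis plan, and its text and Table 1 agree on the method, so the choice is stated and not left open.

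**Conclusion.** The point holds as a modest loss of efficiency in five secondary outcomes. The planned crude comparison is valid, and the primary conclusion is untouched. Under the assumed 16% to 25% mortality and AUC 0.70 to 0.74, the mortality CI would be about 4% to 8% narrower, falling to 1% to 2% at AUC near 0.60. The composite would gain about 3% to 5%, on the further assumption of 9% DVT or PE unrelated to severity.

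The figures come from a correctly specified model with a single score. The contribution of further covariates and of the heparin stratum was not quantified. The direction is the same over the whole range examined; the size cannot be fixed from the documents.

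**What to change.** Before database lock, prespecify for the four mortality outcomes and the composite a marginal RR with 95% CI, standardized from one logistic model with arm, continuous APACHE II, age, admission category and heparin stratum. Report it alongside the planned crude RR and chi-square. Standardizing to a marginal RR keeps the plan's effect measure; a conditional odds ratio should not take its place. Name the single model and the method for its interval in advance, so that no choice remains once data are seen.

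The timing allowed this: 1620 of 2000 patients had been enrolled by January 2018, and the article says its authors stay blinded until recruitment ends and the database is locked.

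The cost is a short addition to the plan, a little extra analysis, and a simple rule for missing baseline scores, such as single imputation of the covariate. No new data collection is needed.
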